## Abstract

**Background:**

The introduction of anti-tumor necrosis factor medications has revolutionized the treatment of psoriasis with achievement of treatment goals (Psoriasis Area and Severity Index score 75, remission) that are not usually met with conventional systemics. Nevertheless, some patients continue to experience persistent disease activity or treatment failure over time. Strategies to optimize treatment outcomes include the use of concomitant methotrexate, which has demonstrated beneficial effects on pharmacokinetics and treatment efficacy in psoriasis and other inflammatory diseases.

**Methods:**

This is an investigator-initiated, multicenter randomized controlled trial (RCT) designed to compare the combination treatment of adalimumab and methotrexate with adalimumab monotherapy in patients with psoriasis. The primary outcome is adalimumab drug survival at week 49. Other outcomes include improvement in disease severity and quality of life, tolerability, and safety. Moreover, anti-adalimumab antibodies and adalimumab serum concentrations will be measured and correlations between genotypes and clinical outcomes will be assessed. Patient recruitment started in March 2014. Up to now, 36 patients have been randomized. Many more patients have been (pre)screened. A total of 93 patients is desired to meet an adequate sample size. In our experience, the main limitation for recruitment is prior adalimumab therapy and intolerability or toxicity for methotrexate in the past.

**Discussion:**

OPTIMAP is the first RCT to examine combination therapy with adalimumab and methotrexate in a psoriasis population. With data derived from this study we expect to provide valuable clinical data on long-term treatment outcomes. These data will be supported by assessment of the impact of concomitant methotrexate on adalimumab pharmacokinetics. Furthermore, the influence of several single nucleotide polymorphisms on adalimumab response will be analyzed in order to support the development of a more personalized approach for this targeted therapy.

**Trial registration:**

NTR4499. Registered on 7 April 2014.

**Electronic supplementary material:**

The online version of this article (doi:10.1186/s13063-017-1777-y) contains supplementary material, which is available to authorized users.

## Background

Adalimumab has been shown to be highly valued by patients with psoriasis due to its profound improvements in disease severity and its favorable safety profile [1, 2]. Although its introduction (together with other anti-tumor necrosis factor (TNF) medications) has majorly advanced psoriasis care, some patients experience persistent disease activity (primary non-responders), treatment failure over time (secondary non-responders), or side effects [3–5]. Several factors have been identified to play a role in primary and secondary non-response to anti-TNFs, including pharmacokinetic factors such as the formation of anti-drug antibodies (immunogenicity) and inter-individual variation in serum drug concentrations as well as pharmacogenetic factors such as the absence or presence of certain single nucleotide polymorphisms (SNPs) affecting drug metabolization [6, 7].

When anti-drug antibodies are formed in patients treated with an anti-TNFα, clearance of the biologic can, to a certain extent, be accelerated depending on the concentration of the anti-drug antibodies [8]. Moreover, anti-drug antibodies can be functionally neutralizing, thereby directly affecting treatment efficacy [9]. Multiple studies observed an association between the formation of anti-adalimumab antibodies, reduced serum levels, and diminished clinical response in psoriasis and other chronic inflammatory diseases [3, 10–13]. In rheumatoid arthritis (RA) and Crohn's disease, concomitant use of methotrexate (MTX) during treatment with certain TNFα inhibitors (adalimumab, infliximab, and golimumab) has been demonstrated to decrease immunogenicity and significantly reduce clearance, resulting in higher systemic exposure and enhanced clinical efficacy [11, 14–18]. Therefore, the use of combination therapy may be beneficial for successful long-term adalimumab treatment. In addition, combination therapy may enable dose reductions of individual agents, thereby decreasing toxicity and improving tolerability and compliance [19]. By targeting unregulated increased cytokine levels associated with inflammatory comorbid conditions, it is hypothesized that combination therapy may also provide a broader benefit to the patient by reducing the risk of, for example, cardiovascular events [20].

On the other hand, combination therapy may theoretically convey an increased risk for serious infections and malignancies.

Currently available evidence on anti-TNFα therapy with MTX in psoriasis is limited to two randomized controlled trials (RCTs) on etanercept with MTX [19, 21, 22] and a few observational studies and case series on other different anti-TNFα agents with MTX [23–25]. The two RCTs on etanercept and MTX provided promising results with superior efficacy of etanercept with MTX compared to etanercept monotherapy. RCTs investigating combined treatment with adalimumab and MTX are lacking [19, 26].

In order to investigate whether adalimumab treatment can be optimized by using concomitant MTX, long-term clinical and pharmacokinetic data on the use of adalimumab in combination with MTX are desired. Additionally, as several polymorphisms have been identified as potential predictors for anti-TNF therapy in psoriasis (e.g., TNFR1B, TNFAIP3, IL12B/IL23R) [6, 27] and other chronic inflammatory diseases (e.g., FcGR and ATG16L1) [28, 29], it will be valuable to detect genetic factors associated with response to adalimumab in order to support personalized care.

### Aims and objectives

The aims and objectives of this trial are:To gain long-term RCT data on the efficacy and safety of adalimumab combined with MTX compared to adalimumab monotherapyTo assess the impact of concomitant MTX on adalimumab immunogenicity and serum concentrationsTo test appropriate candidate genes and correlate genotypes with trial outcomes

## Methods

This is a multicenter RCT reported according to the Standard Protocol Items: Recommendations for Interventional Trials (SPIRIT) guidelines (see Table 1 (SPIRIT table) and Additional file 1 (SPIRIT checklist)). The trial was granted ethics approval by the Academic Medical Center research ethics committee (METC 2013_346). The trial is registered at The Netherlands National Trial Register (trial number: NTR4499) and in the European Clinical Trials Database (EudraCT number: 2013-004918-18). All participants will sign informed consent before participation. The study is being conducted according to the principles of the Declaration of Helsinki and in accordance with the Medical Research Involving Human Subjects Act (WMO) and other relevant guidelines, regulations, and acts.

**Table 1 Tab1:** Timeline of the study according to the SPIRIT guidelines

Time	Screening	Week −2	Week −1	Week 0	Week 3	Week 5	Every 12 weeks from week 13 up to week 145	Early termination
Enrollment								
Informed consent	X							
Demography, medical history	X							
Vital signs and full physical examination	X			X		X	X	X
Psoriasis Area and Severity Index (PASI)	X			X		X	X	X
Eligibility criteria	X							
Laboratory assessments	X		X	X	X	X	X	X
Chest X-ray, Mantoux test, and interferon-gamma release assay (IGRA)	X							
Randomization	X							
Intervention								
Adalimumab (Humira) + MTX		X (MTX)	X (MTX)	X (Humira + MTX)				
Humira monotherapy				X (Humira)				
Assessments								
Laboratory assessments	X		X	X	X	X	X	X
PASI	X			X		X	X	X
Physician global assessment	X			X		X	X	X
Patient global assessment	X			X		X	X	X
Impact on quality of life (Skindex 29 and Dermatology Life Quality Index (DLQI))	X			X		X	X	X
Prior or concomitant therapy	X			X		X	X	X
Adverse events	X			X		X	X	X
Drug adherence				X		X	X	X

### Participants

Patients will be recruited from the outpatient clinics of the Departments of Dermatology of the Academic Medical Center (AMC) Amsterdam, Erasmus University Medical Center (EMC) Rotterdam, and the Radboud University Medical Center (RUMC) Nijmegen. Moreover, other dermatologists will be contacted to recruit and refer eligible patients to the participating centers. Participants must meet the inclusion criteria and none of the exclusion criteria (Table 2) in order to participate. These criteria will be assessed at the screening visit. Potential participants who are deemed ineligible at screening will be allowed a second screening visit if the reason for ineligibility is a temporary status (e.g., latent tuberculosis).

**Table 2 Tab2:** Eligibility criteria

Inclusion	Exclusion
≥18 years Diagnosis of moderate to severe plaque psoriasis (PASI ≥8) Adalimumab naïve Candidate for biologic therapy Willing and able to use adequate contraceptives during the study	History of significant MTX toxicity, intolerability, or contraindication Known liver or kidney malfunction Alcohol abuse Bone marrow hypoplasia, leukocytopenia, thrombocytopenia, or significant anemia Known severe or chronic infections like tuberculosis or HIV Ulcers in the oral cavity or known active ulcers in digestive tract Pregnant or nursing women Need for live vaccinations Use of other immunosuppressive medication (e.g., prednisone, mycophenolate mofetil (Cellcept), cyclosporine (Neoral), sirolimus (Rapamune), systemic tacrolimus (Prograf))

### Interventions

All patients receive adalimumab 40 mg subcutaneously every other week starting 1 week after a loading dose of 80 mg and will be randomized 1:1 to receive either oral MTX 10 mg weekly (combination group) or no addition of MTX (monotherapy group). MTX therapy will be initiated 2 weeks prior to adalimumab therapy, and administration will be followed by folic acid 5 mg 24 hours after MTX intake (see Table 1).

In case of MTX toxicity (e.g., liver toxicity or leukopenia) or intolerability, dosing can be paused (for a maximum of 2 weeks up to four times during the entire study), or the dose can be adjusted to 7.5 mg. Moreover, patients are allowed to switch from oral to subcutaneous administration. In case of adalimumab toxicity or intolerability, dosing can be paused (for a maximum of 2 weeks up to four times during the entire study).

Throughout the study, no systemic anti-psoriatic drugs are allowed for treatment other than the study medication (Table 3). If medically necessary (i.e., to control intolerable psoriasis activity), rescue treatment with topical corticosteroids, vitamin D derivates (calcipotriol/betamethasone or calcitriol), or calcineurin inhibitors may be provided to study patients at the discretion of the investigator after baseline and through week 145 (end of study) (Table 4).

**Table 3 Tab3:** Wash-out periods

Therapy	Wash-out period
Topical therapy	2 weeks
Phototherapy	2 weeks
Conventional systemic therapy/etanercept	4 weeks
Infliximab/ustekinumab	6 weeks

**Table 4 Tab4:** Allowed escape medication

Scalp/palms/soles	Low or high potency corticosteroids, calcitriol/calcipotriol, or a combination
Face and body	Low potency corticosteroids, calcitriol/calcipotriol, or topical tacrolimus 0.1% or 0.03%
inverse psoriasis	Topical tacrolimus 0.1% or 0.03%

### Randomization and blinding

Consecutive patients will be prospectively enrolled and randomly assigned if eligible to either the intervention (adalimumab with MTX) or control (adalimumab monotherapy) group after obtaining informed consent. Each consecutive patient will be assigned a randomization number according to a computer-generated randomization list (ALEA) using random block sizes of 2, 4, 6, and 8 to ensure allocation concealment. Randomization is stratified for TNFα-blocker exposure status to achieve balance with regard to prior TNFα-blocker exposure in the study population.

This is an observer-blinded study. The observer (outcome assessor) will perform clinical outcome assessments of disease severity (Psoriasis Area and Severity Index (PASI) and investigator global assessment (IGA)) at each study visit. The clinician performs all other study procedures and is not blinded. Both clinician and participant know the treatment allocation; as such, no special measures are required to allow for breaking of treatment codes. However, treatment allocation will not be revealed to the recruiting physician until participants’ details and key stratification variables have been irrevocably entered onto the web-based randomization site.

### Endpoints

The primary outcome is adalimumab drug survival (number of patients still on adalimumab treatment) at week 49.

Secondary outcomes are the following:Adalimumab drug survival (number of patients still on adalimumab treatment) at week 145Proportion of patients who reach treatment goals^1^ at week 13, week 25, week 49, and week 145Proportion of patients achieving PASI 75 at weeks 49 and 145Proportion of patients achieving IGA clear or almost clear at weeks 49 and 145Mean improvement in PASI at weeks 49 and 145Proportion of patients with PGA clear or almost clear at weeks 49 and 145Mean improvement in Dermatology Life Quality Index (DLQI) and Skindex at weeks 49 and 145Proportion of patients with (serious) adverse events at weeks 49 and 145Proportion of patients with changes in laboratory assessments at weeks 49 and 145Proportion of patients with (no, low, or high) levels of antibodies at weeks 49 and 145Median adalimumab trough concentrations (mg/L) at weeks 49 and 145Correlation between genetic polymorphisms and adalimumab response

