### Laboratory testing

Blood samples will be collected at each visit (serum samples are collected just before administration of adalimumab (3-day window) to ensure accurate determination of serum through levels) to monitor drug safety, to determine immunogenicity against adalimumab, and to measure adalimumab serum through levels. Samples for serum preparation are kept at room temperature for 1–2 hours for coagulation, followed by centrifugation at 3000 RPM for 15 minutes at room temperature. Supernatant is collected, aliquoted, and stored at −20 °C until further use. Adalimumab serum through levels will be determined using a non-commercial enzyme-linked immunosorbent assay (ELISA, Sanquin, Amsterdam, The Netherlands). Detection of anti-adalimumab antibodies will be performed through a radioimmunoassay (Sanquin). The antibody test will be considered positive when the antibody concentration exceeds 12 AU/mL. Concentrations between 12 and 100 AU/mL will be considered low antibody titers; those above 100 AU/mL will be considered high antibody titers [3].

Additionally, a single blood sample will be collected at screening from which DNA will be collected and stored at −80 °C. As scientific interest in this field is currently increasing, DNA analysis will be performed based upon accumulating data acquired from (ongoing) pharmacogenetic studies.

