### Justification of sample size

A total of 84 patients (randomized 1:1 to concomitant MTX or no MTX) will give the study at least 80% power at a 0.05 two-sided significance level using a two-sample chi-squared test to detect a difference of 28% in drug survival at week 49. We aim to enroll 93 patients to allow for an approximate 10% loss to follow-up. These calculations were performed using Nquery 6.0.2. Due to the lack of data in a psoriasis population, the expected clinically relevant difference in drug survival between both treatment groups was hypothesized based on studies performed in patients with RA. The prevalence of (clinically relevant) anti-drug antibody formation is estimated to be 45% in patients on adalimumab monotherapy (a similar percentage is found in patients with psoriasis [31] and around 17% in patients on adalimumab with low-dose (5–10 mg) MTX after 49 weeks [32]. A clear correlation between antibody formation and treatment failure (with subsequent treatment discontinuation) in patients on adalimumab has been demonstrated [31]. Based on these data, drug survival is estimated to be 83% (100 minus 17) for the experimental group and 55% (100 minus 45) for the control group after 49 weeks of follow-up.

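### The antibody and trough endpoints at weeks 49 and 145 are likely to be observed mainly in patients still on adalimumab, a status that is itself the primary outcome

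*Protocol article*

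**What the plan says.** The second aim of the trial is the effect of concomitant methotrexate on adalimumab immunogenicity and serum concentrations. Two secondary outcomes serve it (protocol article, Endpoints): the proportion of "patients with (no, low, or high) levels of antibodies at weeks 49 and" 145, and the median "adalimumab trough concentrations (mg/L) at weeks 49 and" 145. No denominator is given for either, and nothing is said about patients who stopped before the week in question.

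Laboratory testing states: "Blood samples will be collected at each visit". It adds that serum is taken shortly before an adalimumab administration, within a 3-day window. An antibody test is positive above 12 AU/mL; titres up to 100 AU/mL are low and those above are high. Table 1 marks laboratory assessments at every 12-weekly visit and at a single early-termination visit, with no column after it.

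The sample-size section links antibodies to stopping. It states: "The prevalence of (clinically relevant) anti-drug antibody formation is estimated to be 45% in patients on adalimumab monotherapy". It puts the figure at about 17% with low-dose methotrexate, cites a correlation between antibodies and treatment failure with subsequent discontinuation, and concludes: "drug survival is estimated to be 83% (100 minus 17) for the experimental group and 55% (100 minus 45" for the control group.

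**The concern.** A trough sample presupposes a next dose, so a patient who stopped adalimumab before week 49 has no week-49 trough. An antibody sample at week 49 is possible after stopping, but no schedule for one is shown. As written, both endpoints would probably rest on the patients still being treated.

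Those patients are a selected group. Continuing adalimumab to week 49 is the primary outcome. The plan expects it to differ between arms by 28 points and gives antibody formation as the reason. A comparison among continuers therefore selects on an outcome that the measured quantity is thought to cause, and it would lose antibody-positive patients, more of them from monotherapy. A small difference among continuers could then be read as methotrexate having little effect on immunogenicity when it had prevented antibodies in patients no longer counted. This is a secondary endpoint, but it is the direct measure of a stated aim.

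**Working it through.** **Inputs (Justification of sample size).** Antibody prevalence q is 0.45 on monotherapy and 0.17 on combination. Week-49 drug survival s is 0.55 and 0.83. "A total of 84 patients (randomized 1:1 to concomitant MTX or no MTX") gives 42 per arm.

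**Step 1: the plan's own figure.** The section claims "at least 80% power at a 0.05 two-sided significance level using a two-sample chi-squared test to detect a difference of 28% in drug survival". With the pooled normal approximation, p̄ = (0.55 + 0.83)/2 = 0.69 and

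n = [1.96·√(2·0.69·0.31) + 0.8416·√(0.55·0.45 + 0.83·0.17)]² / 0.28² = (1.282 + 0.525)² / 0.0784 ≈ 41.6, so 42 per arm and 84 in total.

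Power at 42 per arm is 80.4%. The stated size is reproduced.

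**Step 2: what the planning arithmetic implies.** Survival is set to 1 − q in each arm. Numerically, every antibody-positive patient has stopped by week 49 and no other patient has. Of 42 per arm, 42 × 0.55 = 23.1 and 42 × 0.83 = 34.9 remain, none of them antibody-positive.

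**Step 3: general form.** Let f be the share of antibody-positive patients who stop and g the share of antibody-negative patients who stop. Among patients on drug,

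share positive = q(1 − f) / [q(1 − f) + (1 − q)(1 − g)].

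Example with f = 0.75, g = 0: monotherapy 0.1125/(0.1125 + 0.55) = 17.0%; combination 0.0425/(0.0425 + 0.83) = 4.9%.

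If survival is instead held at the plan's 55% and 83%, the share is q(1 − f)/s, and the share of negatives who must then have stopped is g = (1 − s − qf)/(1 − q). Example with f = 0.5: 0.225/0.55 = 40.9% and 0.085/0.83 = 10.2%.

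All values of f below 1 are assumptions; the documents give none. Each pair is monotherapy / combination.

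| Case | f | g | Survival | Positive among on-drug | Difference (points) |
|---|---|---|---|---|---|
| Planning arithmetic taken literally | 100% | 0% / 0% | 55% / 83% | 0% / 0% | 0 |
| Only positives stop | 90% | 0% / 0% | 59.5% / 84.7% | 7.6% / 2.0% | 5.6 |
| Only positives stop | 75% | 0% / 0% | 66.25% / 87.25% | 17.0% / 4.9% | 12.1 |
| Only positives stop | 50% | 0% / 0% | 77.5% / 91.5% | 29.0% / 9.3% | 19.7 |
| Survival held | 90% | 8.2% / 2.0% | 55% / 83% | 8.2% / 2.0% | 6.1 |
| Survival held | 75% | 20.5% / 5.1% | 55% / 83% | 20.5% / 5.1% | 15.3 |
| Survival held | 50% | 40.9% / 10.2% | 55% / 83% | 40.9% / 10.2% | 30.7 |

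**Step 4: the alternative.** If positivity in any sample up to stopping or week 49 counts, and those samples capture it, all 42 per arm contribute: 18.9 vs 7.1 positive, 45% vs 17%, a difference of 28 points. This does not depend on f or g, because stopping no longer removes a patient from the denominator.

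No such calculation is possible for trough, for which the documents give no expected values, or for week 145, for which they give no survival or antibody assumption.

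**The case against.** The strongest reply is that the article nowhere prescribes a comparison restricted to patients on drug. It speaks of a proportion of patients without a denominator. It schedules visits until study completion, and it does not say whether early termination means stopping adalimumab or leaving the study. Antibody sampling after stopping is thus neither described nor excluded, and the denominator may be settled in an analysis plan that is not shown. This stands: a survivors-only analysis is a likely consequence of the schedule, not a stated rule. A denominator chosen later would still leave the endpoint fixed at a week when stopped patients have no trough and may have no antibody sample.

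A reader might infer that the plan predicts 0% vs 0%. The documents do not support that. The text claims a correlation; the one-to-one link exists only in arithmetic used to set the drug-survival effect. The 45% refers to clinically relevant antibodies, whereas the endpoint also counts low titres above 12 AU/mL, and such patients may well continue.

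A reader might also infer that the on-drug comparison is always biased towards no difference. That is not supported either. With survival held at 55% and 83% and half of the positives stopping, the difference is 30.7 points, slightly above 28, because negatives must then also stop, and at different rates by arm (40.9% and 10.2%).

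Finally, a trough level has meaning only during dosing, so an on-treatment median at a fixed week is a legitimate summary. That is accepted, provided it is labelled as conditional.

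**Conclusion.** The concern holds in a limited form. The schedule makes it likely that the week-49 and week-145 antibody and trough endpoints come mainly from patients still on adalimumab, and the sample-size section itself assumes that this status differs by arm because of antibodies. If only those patients are compared, the contrast conditions on a post-randomisation outcome and is not a clean estimate of the methotrexate effect on immunogenicity.

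The size is uncertain. The on-drug difference runs from 0 points (the limiting case) through 5.6 to 12.1 points if 90% to 75% of positives and no others stop, up to 30.7 points in the case that does not shrink, against 28 points when every patient is counted. These results rest on the plan's 45% and 17% and on assumed stopping shares. For trough, the documents support the selection argument but no number. The point is an inexpensive improvement to the measurement of a named aim and does not touch the primary analysis.

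**What to change.** **Antibodies.** Define the endpoint as the highest category (none, low, high) in any sample up to week 49, and separately up to week 145, including the early-termination sample, in all randomised patients who started adalimumab, by randomised arm. Keep the fixed-week proportion among patients on drug as a descriptive figure. State how many randomised patients in each arm never started adalimumab, because methotrexate begins two weeks earlier in one arm only.

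**Trough.** Label the week-49 and week-145 medians as conditional on still being on adalimumab, and give the number on drug in each arm. Report on-treatment trough levels from all visits beside them, including early termination.

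**Clarification.** Say whether early termination means stopping adalimumab or leaving the study, and that the blood taken there includes the antibody and drug-level samples.

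**Cost.** Endpoint and analysis wording only: blood is already drawn at each visit, and Table 1 marks laboratory assessments at early termination.

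**Downside.** Cumulative incidence counts patients who are positive only transiently, and it depends on time under observation: a patient who stops early has fewer samples in which antibodies can be found. The number of samples and the observation time per arm should be reported with it.
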